#### Data collection to document initial adaptations

Several kinds of data will be collected to document the adaptation process and to assess the effectiveness and inclusiveness of the adaptation process. During the initial stage of adaptation (states 1 and 2), we will collect the following data.
*Qualitative interviews with parents on parenting norms.* A series of 24 semi-structured interviews with parents from the targeted groups will be conducted to assess parenting norms and practices that may need to be incorporated into the curriculum modifications. Questions focused on how parents typically spend time with children, enjoyable activities, how the partner and extended family typically interacts with children, how decisions are made in the household, what the rules for behavior are in the household and how they are established and enforced, reward and discipline practices, challenges to raising children in the U.S., and how raising children is different in the U.S. compared to the home country.*Documentation of changes.* Graduate assistants who are not part of the adaptation team will attend all of the adaptation team meetings to take notes and record suggested and agreed upon adaptations.*Initial adaptation needs scale.* Prior to beginning adaptations, the team was provided an overview of the SafeCare intervention. Members of the team who will deliver services (i.e., providers from organizations and community health workers) will be asked to complete a nine-item survey to assess their perceptions regarding the need for adaptations. The scale was developed by Finley and colleagues [41] and modified slightly here to assess the need for adaptations, fit of the intervention for their client, mismatches between elements of SafeCare and clients, and the need to adapt the delivery methods (e.g., by adding other interventions, changing the setting, etc.).*Inclusion survey after each meeting.* After each meeting of the adaptation team, each member of the team will be invited to complete a six-item survey to assess strengths and challenges of the meeting, feelings of comfort during the meeting, overall effectiveness of the meeting, as well as any changes they would like to see in future meetings. The intent of the survey is to gauge the extent to which different types of members of the adaptation team felt heard and included throughout the process.*Qualitative interviews with adaptation team members.* Upon completion of the initial adaptation process, the research team will interview all members of the adaptation team using a semi-structured format. Questions focused on the adapted materials (e.g., in what ways are they more appropriate for the targeted populations) and the adaptation process (e.g., perceptions of inclusion, whether certain perspective were not considered, etc.).*Adaptations made.* We will catalog and describe the adaptations made for each of the targeted communities. This will include adaptations to the curriculum itself and to the implementation process.

#### Adaptation process once implementation begins

Once the curriculum is adapted and implementation begins, the adaptation team will continue to meet to discuss implementation and client-driven adaptations. The initial implementation of SafeCare will be carefully monitored in line with Barrera and Castro’s^111^ third and fourth phases, the *preliminary adaptation test* and *adaptation refinement*. The preliminary adaptation test phase typically involves pilot participants. Here, because we expect adaptations to be ongoing and a key question in the study, we will not consider the initial participants pilot participants, but will simply monitor implementation closely as the first participants are enrolled. The goal of the third and fourth phases are to carefully gauge participant reactions to the intervention, discuss any major problems, and make refinements as needed. The adaptation team will continue to meet on a regular basis (biweekly or monthly) depending on the frequency of sessions. Meetings will be coordinated by NSTRC training staff, and as recommended by Barrera and Castro [7] decisions for further adaptations will be made by the team of model experts and cultural experts. If further protocol modifications are needed, we will convene trainees for additional training session.

#### Analyses

Analyses of data for Aim 1 will be primarily descriptive with the goal of understanding what adaptations were made and to evaluate the process. We will document and categorize adaptations made to the curriculum and implementation process. To assess the process, we will compute means and standard deviations of the quantitative measures collected (initial adaptation needs and the inclusion survey) and conduct qualitative coding of adaptation team members perceptions of the process.

### Aim 2

Aim 2 of this project is to examine SafeCare implementation using two different methods: standard implementation (SI) by community-based agencies and task-shifted (TS) implementation in which community members are trained deliver SafeCare directly to families. The study design is a quasi-experimental design in which we will examine both implementation metrics and family outcomes across the two implementation types.

#### Standard implementation

Standard implementation will be carried out by three refugee resettlement agencies Each of these agencies is well-established and has operated in Clarkston for several years. Services typically offered as part of resettlement include: welcoming newly arrived refugees at the airport, assistance with housing and food, medical care, legal assistance, employment, language and cultural integration, and enrolling children in school. While these agencies are focused on supporting new arrivals to self-sufficiency within the first 6 month, they also offer ongoing services to the refugee and immigrant community in Clarkston to promote ongoing adjustment and self-sufficiency.

Standard implementation of SafeCare-PCI at the three refugee resettlement agencies will be conducted by current employees of those agencies who will be trained to deliver SafeCare-PCI. Agencies will receive funding from the project to deliver services, and they must determine who is best suited for carrying out these activities and how other tasks are to be managed to allow for time to deliver the new service. The same agency staff will be part of the adaptation team described above. Agencies will also determine how to ‘package’ services to clients which may affect implementation of the newly adopted service. By packaging, we mean when to offer it, what to offer with it, and whether the new service replaces any existing services.

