### Study aims

There are two primary aims of the study. The first is focused on curriculum adaptations to create culturally appropriate content of a behaviorally-based parenting model, SafeCare©, to be implemented in a community of refugees and immigrants. An adaptation team consisting of model experts, community members, and service providers will adapt SafeCare for Afghan, Burmese, and the Congolese communities. The second aim is focused on an exploration of task shifting by testing two approaches to a community-based SafeCare implementation: (1) implementation as usual via delivery by providers at community-based agencies and (2) a task-shifted approach in which services are delivered by citizens of the community who do not necessarily possess professional backgrounds and education or experience. As previously mentioned, the traditional SafeCare implementation approach is commensurate with Deller’s [36] recommendations for key components pertaining to the training and support of a successful task shifting implementation. Thus, the primary difference in this aim will be about *who* is delivering the program. We will examine implementation metrics including clients served, model fidelity, adaptations, client skill acquisition, and cultural acceptability. We will also examine family outcomes for families served in each method including parenting behavior, parent-child relationship, parenting stress, and child social and emotional health.

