#### Task-shifted implementation

Task-shifted implementation will be conducted by community health workers (CHWs). CHWs are individuals who are citizens of the Clarkston community and members of the ethnic groups being served and will be hired directly to be part of the project and paid for recruitment and delivery of SafeCare-PCI. As noted above, these CHWs will serve as part of the adaptation team. CHWs are expected to provide their own transportation to sessions.

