#### Referral sources

Referral sources may vary for standard and task-shifted implementation. Recruitment of clients at standard implementation sites will be done primarily from the pool of existing clients already served by those agencies, and referrals received for other services. The resettlement agencies have a range of existing programs and services they offer to families, and families with children in the target age range already being served will be offered SafeCare services. Additional referrals may come from governmental organizations, social service organizations, healthcare providers, and ethnic group organizations.

Recruitment and referrals for services to be delivered by CHWs will be facilitated by the administrative structure of the project. That is, project staff will make connections with community-based referral agencies, advertise the study and services with the help of project stakeholders and community leaders, and direct interested participants to the CHW’s for the service. CHWs are expected to have strong connections to community organizations, social service and health agencies, childcare providers, and ethnic organizations, and those connections should facilitate service referrals. All recruitment efforts will describe the intervention service as a program designed “to build a positive relationship with your child and promote healthy development to be ready for school.”

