### Innovation

There are several innovative aspects to this project. First, though standard evidence-based practices such as SafeCare are adapted regularly for disparate populations, this project is simultaneously adapting the curriculum for three groups and delivering it to populations of new Americans. The adaptation process we will engage in is unique in that it will be conducted by a team consisting of model experts, service providers, and community members who will create a culturally relevant curriculum and delivery process. Typically, adaptations to programs are done with a single ethnic group; here we will simultaneously adapt the intervention protocol for three ethnic groups. We will document the adaptations that occur in the field based on consumer demand.

A second major innovation is the application of the task shifting approach in this setting. Task shifting, or using a lay workforce, has been successfully implemented in low income countries to address a range of issues including HIV and mental health problems. Task shifting has been used in the U.S. to address workforce shortage issues (e.g., responsibility for prescribing some drugs has been shifted from physicians to nurse-practitioners), but, to our knowledge, it has not been implemented using a workforce of lay professionals trained to implement preventive family-based or mental health services in the U. S with highly diverse populations. This study will allow us to carefully monitor and document the successes, challenges, and barriers of a task-shifted workforce relative to a standard workforce. We will also track family outcomes to determine if differences are seen between implementation by a standard workforce relative to a task-shifted workforce. This will provide new information on (1) whether an evidence-based intervention like SafeCare can be delivered with fidelity and high consumer satisfaction, and (2) whether family outcomes differ for a task-shifted implementation of SafeCare compared to a standard implementation.

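### Aim 2 is described as a contrast of who delivers SafeCare, but only the standard-implementation agencies may decide what accompanies or is replaced by it, so a difference in family outcomes cannot be credited to provider type alone

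*Protocol article*

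**What the plan says.** **The contrast.** In Study aims, the article argues that SafeCare's usual training and support already suit task shifting and concludes that "the primary difference in this aim will be about *who* is delivering the program". The Innovation section says the study will show "whether family outcomes differ for a task-shifted implementation of SafeCare compared to a standard implementation", and describes this as a comparison of a standard with a task-shifted workforce.

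**The SI arm.** In Standard implementation, three resettlement agencies deliver SafeCare through their own staff. They have discretion over its setting: "Agencies will also determine how to ‘package’ services to clients which may affect implementation of the newly adopted service". The term is then defined: "By packaging, we mean when to offer it, what to offer with it, and whether the new service replaces any existing services". The agencies' typical services include "assistance with housing and food, medical care, legal assistance, employment, language and cultural integration, and enrolling children in school". Under Referral sources, "Recruitment of clients at standard implementation sites will be done primarily from the pool of existing clients already served by those agencies".

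**The TS arm.** In Task-shifted implementation, CHWs "will be hired directly to be part of the project and paid for recruitment and delivery of SafeCare-PCI". No packaging choice is described for them.

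**Measurement and analysis.** Assessment of family outcomes lists the interview measures, and none is a record of other services received. Under Analyses, Family outcomes, implementation group is the primary independent variable, and the primary outcomes are parent skills, the parent-child relationship and parenting stress. The Limitations section does not mention packaging.

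**The concern.** If the arms differ in who delivers the programme and also in what surrounds it, the group coefficient mixes the two. Help with housing, employment or language could plausibly move parenting stress, which is a primary outcome, or the likelihood of completing the six sessions. An SI advantage might then come from accompanying services and not from professional staff. Equally, services bundled with SafeCare in SI could mask a benefit of task shifting, and dropping a usual service to make room for SafeCare could work the other way.

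This is separate from the different recruitment routes. Those concern which families enter each arm, and baseline adjustment can address them in part. Packaging acts after enrolment, so baseline covariates do not remove it. What is at stake is the sentence Aim 2 may write about family outcomes, namely whether it concerns provider type or two whole ways of delivering the programme.

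**Working it through.** **Step 1: set the passages side by side.**

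| Feature | SI arm | TS arm |
|---|---|---|
| Training | All providers trained together | Same |
| Who delivers | Agency employees | CHWs from the ethnic communities |
| Timing of the offer, accompanying services, services replaced | Decided by the three agencies | No provision described |
| Main source of families | Existing agency clients | Community referral and advertising |

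Training is common to both arms, which supports the Study aims sentence. The third row is a second difference between the arms, it may vary across the three agencies, and the protocol itself concedes that it can matter.

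**Step 2: look for anything that separates packaging from provider type.**

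- Assessment of implementation outcomes will document planned and ad-hoc adaptations to the implementation process for each arm. This may capture some packaging decisions, but as a descriptive catalogue and not as a record of what each family received.
- Assessment of family outcomes includes family resources, concrete support and post-migration difficulties. These measure needs and stressors, not receipt of services.
- The covariate rule under Analyses, Implementation metrics is triggered by baseline differences, and packaging comes later.

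None of these separates the two.

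**Step 3: the protocol's own figure.** Family outcomes gives detectable differences of d = .35–.45 with 240 families and up to 20% attrition. Alpha and power are not stated. Assuming two-sided 5% and 80% power, the detectable d is (1.960 + 0.842) × √(2/n):

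- n = 120 per arm: 2.802 × 0.1291 = 0.362
- n = 96 per arm (120 × 0.8): 2.802 × 0.1443 = 0.404

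These fall inside the stated range, and the figure is not in dispute.

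**Step 4: an illustration of scale.** The documents give no figure for the effect of other services, so the shifts below are assumptions. Suppose provider type has no effect, families are independent, and other services shift the SI mean by b SD. With s = b / √(2/n), the chance of a significant two-sided 5% result is 1 − Φ(1.96 − s) + Φ(−1.96 − s).

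| b (SD) | n = 120 per arm | n = 96 per arm |
|---|---|---|
| 0 | 5% | 5% |
| 0.10 | 12% | 11% |
| 0.15 | 21% | 18% |
| 0.20 | 34% | 28% |

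For b = 0.15 and n = 120: s = 0.15 / 0.1291 = 1.162, so the probability is 1 − Φ(0.798) + Φ(−3.122) ≈ 0.212 + 0.001 = 0.213.

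Shifts well below the detectable range would therefore affect the comparison. The same table would follow from any bias of the same size. It shows what would matter, not what will occur.

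**The case against.** The strongest reply is that packaging belongs to the strategy under test. Study aims describes SI as implementation as usual by agency providers, and an agency deciding how to offer a service is part of that. Study aims calls provider type the primary difference and does not say it is the only one. The Family outcomes contrast is between implementation groups, the article calls this primarily an implementation study, and it openly discloses the packaging discretion. This stands. A reader might infer that the protocol contradicts itself on what SI families receive, but the wording does not go that far. Accepting the reply still means that the contrast is agency delivery with its packaging versus CHW delivery, and the wording about who delivers and about workforce should say so.

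A reader might also infer that TS families receive SafeCare alone. The documents do not support this. The Task-shifted implementation section says what CHWs are paid to do, not what families otherwise use. The agencies offer ongoing services to the wider refugee and immigrant community in Clarkston, CHWs are expected to have links with social service and health agencies, and team meetings cover referrals for families' other problems. The difference between arms in services received could be small and could go either way.

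Part of SI families' service use also predates baseline, because most are existing clients. That part belongs to the recruitment difference. Only what changes after enrolment is at issue here.

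Finally, a condensed article may leave a questionnaire item to a fuller document, so the absence of a service-receipt item is weak evidence on its own. The point rests on two things the article does state: discretion given to one arm, and a conclusion worded by provider type.

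**Conclusion.** The point holds as a limit on attribution. The stated contrast is narrower than the one the design delivers, and as written an SI versus TS difference in family outcomes cannot be attributed to provider type alone. The sections are in tension and need reconciling.

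It would go too far to infer that the comparison is shown to be biased. The documents give no size for any effect of other services and leave its direction open. The rejection rates of 12%, 21% and 34% at 120 per arm rest wholly on assumed shifts, no provider effect, independent families and a two-sided 5% test. The sample size and the stated detectable difference are unaffected. This is an inexpensive improvement that changes what Aim 2 can conclude.

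**What to change.** 1. Reconcile Study aims, Standard implementation and Innovation. Define the Aim 2 contrast as agency delivery with its own packaging versus CHW delivery, and limit the conclusion on family outcomes to that contrast.
2. State in Limitations that provider type and packaging cannot be separated.
3. Add a short item to the post-intervention and 6-month interviews, for families in both arms, on other services received and on any usual service that SafeCare replaced. Report it by arm and by agency.
4. Label any analysis using these answers as exploratory. They are post-enrolment variables, and if packaging is part of SI, adjusting for them or restricting on them removes part of the effect under study. Such an analysis should not be used to correct the main comparison.

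The cost is a few wording changes and slightly longer interviews at two visits already planned. None of this requires telling the agencies how to offer their services, and the sample size stays the same.

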#### Task-shifted implementation

Task-shifted implementation will be conducted by community health workers (CHWs). CHWs are individuals who are citizens of the Clarkston community and members of the ethnic groups being served and will be hired directly to be part of the project and paid for recruitment and delivery of SafeCare-PCI. As noted above, these CHWs will serve as part of the adaptation team. CHWs are expected to provide their own transportation to sessions.

#### Training and support in delivering SafeCare

All providers will undergo training to deliver SafeCare and will be trained together by the NSTRC using its standard training practices [81, 93]. Training in the full SafeCare model is typically 4 days of face-to-face workshop followed by extensive individual coaching with group-based team support. Coaching typically consists of in-person monitoring or a review of recorded sessions scored for fidelity and followed by feedback to the provider. Team meetings are typically held bi-weekly or monthly depending on the team need. Issues discussed during team meetings include general implementation issues including referrals and recruitment, client fit with the intervention, general response to the intervention, adaptations needed, and other needed services.

Because this study included only one of the SafeCare modules, training is planned for 2 days of workshop with follow up coaching. The coaching process may need to be adapted depending on how implementation is conducted. For example, review of recordings will not be possible if services are delivered in the family’s native language (as we expect it will). In such a case, the coaching process will be adapted; for example, it may include self-assessments, coaches listening to sessions with an interpreter, providers delivering a session in English to an English-speaking family. We will work with the team to develop the most feasible and rigorous process possible.

Monthly team meetings will be held with each of the three implementing agencies and with the CHW’s together. The goal of these meetings is to build cohesion among the team and discuss implementation issues external to the individual delivery of SafeCare. These issues include referrals and client flow, when clients are not appropriate for SafeCare, referrals for concomitant problems families experience, data collection, and any other issues raised by service providers.

